#### Clinician CATI

Chi square tests will be used to compare preventive care provision, and attitudes and beliefs towards preventive care prior to and following the intervention.

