#### Clients

Clients eligible for participation in the CATI interviews will be those who: are 18 years or older; have attended at least one face-to-face individual appointment with a community mental health clinician within the previous two weeks; have not previously been selected to participate; and have not been identified by their clinician as inappropriate to contact. Additional client eligibility criteria will be assessed upon phone contact and will include: English speaking; not participating in any other surveys regarding health behaviors or care received at community health services; not living in aged care facilities or jail; and being physically and mentally capable of responding to the survey items.

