#### Clinicians

All clinicians within eligible services will receive the intervention. This includes multidisciplinary teams of psychiatrists, psychologists, social workers, dieticians, nurses, and occupational therapists. All clinicians who have had a minimum of 10 individual face-to-face appointments with adult clients within the two months prior to the survey, have been employed for a minimum of three months, and are not contractors are eligible for participation in the CATI interviews.

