#### Clinicians

Clinician surveys will be undertaken pre and post the intervention delivery for each of the two groups. All eligible community mental health clinicians providing care to clients at the community mental health services (approx. n = 200) will be identified through electronic medical records and will be invited to participate in the data collection.

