#### Preventive care delivery

On a scale of 0% to 100%, clinicians will be asked to estimate over the previous two months the proportion of new adult clients they provided with the following:

1. Assessment: the proportion for which they assessed their smoking status, fruit and vegetable intake, alcohol consumption, and physical activity;

2. Brief Advice: For clients with health risk behaviors, the proportion to which they provided brief advice to modify that behavior(s); and

3. Referral: For clients with health risk behavior(s), the proportion they spoke to about the telephone support services, the proportion they arranged for a telephone support service to call them, the proportion they recommended speak to their GP or Aboriginal Medical Service about that behavior(s), the proportion they advised to use any other supports to make changes to their health behavior(s), and the proportion they offered to send a summary of their health risks behavior(s) to their GP or Aboriginal Medical Service.

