#### Attitudes and beliefs towards preventive care

Clinicians will be asked to respond on a five-point Likert scale their agreement with a number of statements related to their attitudes and beliefs towards providing preventive care to their clients (strongly disagree to strongly agree). Items will relate to: whether clients find preventive care acceptable, clinician confidence in providing preventive care, availability of services to refer clients to, whether clients will change their behaviors as a result of the care they provide, management support regarding the delivery of preventive care, knowledge and skills, role congruence, time available to provide preventive care, whether preventive care will jeopardize relationships with clients, and whether clients are interested in changing health behaviors.

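### Chi-square tests fit the clinician survey poorly: they require the 0–100% estimates to be categorised and ignore that an unknown share of clinicians answers both rounds, which costs power

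*Protocol article*

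**What the plan says.** The Statistical analysis section, under Clinician CATI, gives one method for both kinds of clinician outcome: "Chi square tests will be used to compare preventive care provision, and attitudes and beliefs towards preventive care prior to and following the intervention".

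The measures are described earlier. For provision: "On a scale of 0% to 100%, clinicians will be asked to estimate over the previous two months the proportion of new adult clients" who received each element of care (Measures: clinician CATI, Preventive care delivery). For attitudes: "Clinicians will be asked to respond on a five-point Likert scale their agreement with a number of statements" (Attitudes and beliefs towards preventive care).

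On timing, Recruitment (Clinicians) says: "Clinician surveys will be undertaken pre and post the intervention delivery for each of the two groups". The same section invites every eligible clinician, about 200 in all. The eligibility rules under Participants (Clinicians) cover recent appointments, length of employment and contractor status. They do not exclude anyone who took part in an earlier round. The client rules do, since clients must "have not previously been selected to participate".

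Study design and setting describes the clinician interviews as a supplement to the client data. It also counts a rise in clinician-reported provision as part of how effectiveness will be shown.

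**The concern.** Two features of the stated test do not match the stated data. First, a chi-square test compares counts in categories, so a percentage estimate has to be cut into categories before the test can be run, and the cutting discards information. Second, the ordinary chi-square test assumes that the two rounds are made up of different, independent respondents. Here the whole workforce is approached twice, about 12 months apart, so some clinicians will contribute to both rounds. The protocol's argument that client clustering needs no adjustment rests on random sampling of clients and does not carry over to clinicians.

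At stake is the precision of the clinician comparison. The pool is limited to the clinicians employed in the participating services, so lost precision cannot be bought back by recruiting more.

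**Working it through.** **Plan figures.** The protocol gives no sample size, power or detectable difference for the clinician survey, so there is nothing to reproduce on this point. Its only power statements concern clients. A two-sided two-proportion calculation at alpha 0.0167 gives 79.1% for 1,040 against 1,040 (50% to 57%) and 80.3% for 520 against 520 (50% to 60%). Both agree closely with the stated 80%, and neither bears on the clinician analysis.

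**Inputs.** From the protocol: about 200 clinicians invited, surveyed before and after. Assumed, because the protocol does not give them: 200 responders in each round, an outcome dichotomised near 50%, two-sided alpha 0.05, power 80%, overlap f (share of responders common to both rounds), and within-clinician correlation r.

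**Step 1, unpaired test.** SE = √(2 × 0.5 × 0.5 / 200) = √0.0025 = 0.05. Detectable difference = (1.96 + 0.84) × 0.05 = 0.14, or 14.0 points.

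**Step 2, paired analysis with full overlap.** The variance is multiplied by (1 − r), so the detectable difference is 14.0 × √(1 − r):
- r = 0.3: 14.0 × 0.837 = 11.7 points
- r = 0.5: 14.0 × 0.707 = 9.9 points
- r = 0.7: 14.0 × 0.548 = 7.7 points

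**Step 3, partial overlap.** For the simple before/after difference using all respondents, with the covariance counted, the variance factor is (1 − f × r):
- f = 0.8, r = 0.3: 14.0 × √0.76 = 12.2 points
- f = 0.8, r = 0.5: 14.0 × √0.60 = 10.8 points
- f = 0.5, r = 0.3: 14.0 × √0.85 = 12.9 points
- f = 0.5, r = 0.5: 14.0 × √0.75 = 12.1 points

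Over f = 0.5 to 1.0 and r = 0.3 to 0.5, the unpaired test overstates the variance by 1/(1 − f × r), from 1/0.85 = 1.18 to 1/0.50 = 2.0 times.

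**Step 4, response.** If only half of the 200 respond in each round, every figure above is multiplied by √2. The unpaired 14.0 points becomes 19.8.

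**Step 5, direction of the error.** A simulation with 200 per round (20,000 runs per setting, baseline 50%) compared the unpaired chi-square test with McNemar's test on the matched pairs only:

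| Overlap | r | Chi-square type I error | Chi-square power, 50% to 60% | McNemar power, 50% to 60% |
|---|---|---|---|---|
| 50% | 0.3 | 3.5% | 53% | 39% |
| 50% | 0.5 | 2.5% | 53% | 53% |
| 80% | 0.3 | 2.7% | 52% | 57% |
| 80% | 0.5 | 1.3% | 53% | 72% |
| 100% | 0.3 | 2.1% | 53% | 67% |
| 100% | 0.5 | 0.7% | 53% | 81% |

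The chi-square test stays below its nominal 5% throughout. McNemar's test holds about 5% but drops everyone who answered only once. At 50% overlap it therefore gains nothing, which argues for a model that uses all responses.

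**Step 6, categorisation.** For scale only: a median split of a normally distributed measure keeps 2/π = 0.64 of the information. The protocol plans no particular split, and estimates bounded at 0 and 100 need not be normal, so the loss here could differ.

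**The case against.** The strongest reply is that this is an efficiency point about a supplementary survey. All three primary endpoints come from the client interviews. The article is condensed, and cut-points or a paired form could be set out in a fuller plan; McNemar's test is itself a chi-square test. The overlap is not stated. About 200 is the number invited, not the number responding, and eligibility is tied to recent activity ("All clinicians who have had a minimum of 10 individual face-to-face appointments with adult clients within the two months prior to the survey"), so membership can change over the 12 months.

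Much of this stands, and it rules out several stronger readings that a reader might infer:
- **That the test could manufacture a false finding of effectiveness.** With positive correlation its error rate is below nominal.
- **That largely the same 200 people answer twice.** Substantial overlap is a reasonable inference from inviting the whole workforce, but the documents give no figure for it.
- **That the missing cut-point is itself an error.** An article commonly leaves such detail to the full plan.
- **That a chi-square test on five-point ratings is invalid.** It is valid. Ignoring the order costs sensitivity only, and attitudes are not part of the stated demonstration of effectiveness.
- **That clinicians with no new clients would be scored 0%.** Nothing in the protocol says so.

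The reply does not remove the mismatch. The test named is the only analysis given, nothing indicates a paired form, and any cut-point would still discard information from the percentage scale.

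**Conclusion.** The concern holds as a poorly fitting stated analysis, and it should be changed. Followed as written, the clinician comparison categorises a percentage outcome and ignores repeated responses. The result is over-wide intervals and lost power. Ignoring the pairing raises the detectable difference to about 14 points, from 11.7 to 7.7 with full overlap and r = 0.3 to 0.7, or from 12.9 to 12.1 with half overlap and r = 0.3 to 0.5. These figures rest on 200 responders per round, a dichotomised outcome near 50% and assumed correlations. The full-overlap values are a best case. The error is conservative, and the client-reported primary endpoints are not affected.

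**What to change.** For the 0–100% items, replace the chi-square test with a GEE with robust standard errors, or a mixed model suited to bounded percentages. Keep the original scale, with period and group as fixed effects and clinician as the cluster, and include all respondents whether surveyed once or twice. An ordinal version for the five-point ratings is optional.

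The cost is a change of analysis wording plus linkage of each clinician's two responses. Clinicians are identified through the medical record system, and their service and discipline are taken from it, so linkage looks feasible. Under Trial status, however, the intervention is already underway in the second group, so both pre-intervention rounds have probably been collected. Whether identifiers were kept is not stated. If the rounds cannot be linked, use an unpaired comparison on the original scale and report that its intervals are conservative. That fallback keeps the information in the percentage scale but gives up the gain from pairing.

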### Ethics approval

Ethical approval to conduct the study has been obtained from the Hunter New England Human Research Ethics Committee (approval No. 09/06/17/4.03) and University of Newcastle Human Research Ethics Committee (approval No. H-2010-1116).

### Trial status

The intervention is currently underway within the second group of services.

## Discussion

To the authors’ knowledge, this is the first study to assess the effectiveness of a multi-strategic clinical practice change intervention in increasing clinician provision of preventive care for behavioral risk factors of chronic disease across a network of community mental health services. This study is an important step towards redressing the disparity in preventable health outcomes for those with mental illness, through the provision of a potentially sustainable practice change intervention aiming to improve clinical care for four behavioral health risk factors that contribute substantially to the increased rates of chronic disease morbidity and mortality experienced by this group. The results will inform future policy and practice regarding the ability of clinicians within mental health settings to improve preventive care provision as a result of such interventions.

## Abbreviations

CATI: Computer Assisted Telephone Interview; GP: General Practitioner; NSW: New South Wales.
